#### Attitudinal

##### Overview

Given the wide divergence in the definition of antigay bias or homophobia, several scales have been developed across time [18] and will be used in this research.

##### Attitudes Toward Lesbians and Gay Men Scale

This 10-item scale measures beliefs and attitudes toward gay men and lesbians (“Sex between two men is just plain wrong” and “Female homosexuality is a perversion”) [19]. Items are rated on a Likert scale from 1 (strongly disagree) to 5 (strongly agree). After reverse coding 4 items, scores will be averaged into a final score with higher values denoting more negative attitudes.

##### Homophobia Scale

This 25-item scale measures attitudes but also social avoidance and aggression toward gay people (“If I discovered a friend was gay I would end the friendship” and “I tease and make jokes about gay people”) [20]. Items are rated from 1 (strongly disagree) to 5 (strongly agree) on a Likert scale. After reverse coding 9 items, scores will be averaged into a final score with higher values denoting more negative attitudes.

##### Attitudes Toward Homosexuals Scale

This 12-item scale measures attitudes toward gay people (“Homosexuality is disgusting in the eyes of God” and “If I can, I prefer to not be in the company of homosexuals”) [21]. Items are rated from 1 (strongly disagree) to 5 (strongly agree) Likert scale. After reverse coding 5 items, scores will be averaged into a final score with higher values denoting more negative attitudes.

#### Behavioral

##### Behavioral Intentions

This 16-item scale measures intentions for supportive professional behaviors that teachers would perform in the classroom (“I would talk with a student about questions regarding sexual orientation” and “I would have books about gay and lesbian issues in my classroom”) [22,23]. Items are rated on a Likert scale from 1 (strongly disagree) to 5 (strongly agree). Scores will be averaged into a final score with higher values denoting more willingness to engage in LGBT+ supportive behaviors in the classroom.

##### Self-Efficacy

This 10-item scale adapted the original scale to working with LGBT+ students in the school context (“If I try hard, I can solve difficult issues related to LGBT+ students” and “I can deal with unexpected situations that arise with LGBT+ students”) [24]. Items were rated from 1 (Not at all true for me) to 4 (Perfectly true for me). Scores will be averaged into a final score with higher values denoting more self-efficacy in dealing with LGBT+-related behaviors in the classroom.

#### Cognitive: Factual Knowledge About LGBT+ Issues

We constructed 7 items based on training content to assess participants’ knowledge about LGBT+ issues (“Gender is a biological construct, unrelated to cultural associations” and “Heterosexual youth are 1.5 to 3 times more likely to attempt suicide compared to LGBT+ youth”). Items are rated as true or false, and a final score will be computed by adding up the number of correct responses, with higher scores denoting more knowledge about LGBT+ issues.

#### Affective

##### Feeling Thermometer (1 Item Each for Gay, Lesbian, and Bisexual)

We will use a feeling thermometer [25] to assess participants’ feelings toward gay, lesbian, and bisexual people by asking them to rate how they feel about each group using a slider thermometer scale from 0 (very negative feeling) to 100 (very positive feeling).

##### Perspective Taking

This 5-item measure assesses the extent to which participants take the perspective of LGBT+ people (“Can you imagine how an LGBT+ person feels?” and “Do you have an understanding of issues that are important for LGBT+ people”) on a scale from 1 (Never) to 5 (All the time) [26]. Scores will be computed by averaging the 5 items, with higher final scores denoting more perspective-taking.

##### Intergroup Disgust Sensitivity

We adapted this 7-item scale to measure repulsion toward LGBT+ groups (“I feel disgusted when people with a different sexual orientation invade my personal space” and “After shaking hands with someone who has a different sexual orientation, even if their hands were clean, I would want to wash my hands.”) [27]. Items are rated from 1 (strongly disagree) to 5 (strongly agree) on a Likert scale. After reverse scoring 1 item, scores will be averaged into a final score with higher values denoting more disgust toward LGBT+ outgroups.

##### Intergroup Anxiety

This 10-item scale measures anxiety-related emotions when interacting with people of another sexual orientation by asking them to rate their likelihood of feeling several emotions (embarrassed, unsure, irritated, suspicious, etc) on a scale from 1 (not at all) to 10 (extremely) [28]. A total of 2 scores will be computed, 1 for positive emotions and another for negative emotions.

##### Toronto Empathy Questionnaire

This 16-item scale measures the general tendency to empathize with other people (“It upsets me to see someone being treated disrespectfully” and “I find that I am ‘in tune’ with other people’s moods”) [29,30]. Items are rated on a Likert scale from 1 (strongly disagree) to 5 (strongly agree). After reverse scoring 7 items, scores will be averaged into a final score with higher values denoting more empathy.

#### Demographic and Control Variables

##### Demographics

It consists of age, gender, and sexual orientation.

##### Contact With LGBT+ People

We will ask participants how often they have contact (eg, talk) with a gay man, a lesbian woman, a bisexual woman or man, or a transgender person on a scale from 1 (almost daily) to 6 (never).

##### Religiosity

Religiosity (Duke University Religion Index) [31] is a 5-item scale measure of religious involvement, measuring organizational religious activity, nonorganizational religious activity, and intrinsic religiosity (or subjective religiosity). Responses are averaged in 1 single score with higher scores denoting more religiosity.

##### Ideology

Ideology was measured by asking people to indicate their political orientation on a 100-point sliding scale from 0 (very conservative) to 50 (center) to 100 (very liberal or progressive).

### Statistical Analysis

#### Power

To determine our sample size, we conducted a power analysis using an average effect size of *d*=0.66 computed from Bartoş et al’s [9] meta-analysis to ensure a statistical power of 0.80. The analysis indicated a sample of 122, but we aim to overrecruit, if possible, up to 200 participants given multiple outcomes. We do not have a stopping rule—we will recruit until all interested participants are given the chance to participate within 1 of the 17 sessions posted.

#### Data Exclusion

We will use data from all participants who completed their participation in the study, without any exclusions. Before computing final scores for each outcome variable, we will ensure sufficient reliability using Cronbach α, using a threshold of 0.70. To test our hypotheses, we will perform a series of 1-way between-subjects ANOVAs to compare attitudinal, cognitive, behavioral, and affective outcomes between the participants in the experimental and control conditions. For the effective measures we will perform the analyses (1) while controlling for contact with LBGT+ individuals and (2) separately by LGBT+ status (given the nature of the measures). We will report *F* test and *P* values, as well as all descriptive statistics (n, mean, and SD). We will also compute Cohen *d* for estimating the effect size, using means and SDs. Violin plots in R ggplot2 will also be included to visually represent means, CIs, as well as score distributions for each outcome.

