**Methods:**

A sample of 175 school teachers will be randomly assigned to either the control or experimental group. The experimental group participants will receive the intervention first and then complete the outcome measures, whereas the control group will complete the outcome measures first and then receive the intervention. The 1-hour multimedia intervention is developed for internet-based delivery under controlled conditions. It includes 2 interactive exercises, 2 recorded presentations, animations, and testimonies from LGBT+ individuals. Data for attitudinal, behavioral, cognitive, and affective measures will be collected during the same session (before or after the intervention, depending on the condition). We also plan to conduct a brief mixed methods follow-up study at 6 to 8 months post participation to investigate potential long-term effects of training. However, due to attrition and lack of experimental control (all participants will have completed the intervention, regardless of the condition), these data will be analyzed and reported separately using a mixed methods approach.

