**Self-efficacy**			
	Writing exercise, 5 minutes	Duration: 5 minutes 00 second Timestamps: 43.45-48:45	Writing prompt: “Imagine now that, as a teacher, you are interacting with the student you previously imagined. For example, the student asks for your help in a discussion after class. Knowing what you know now about the LGBT+ community and how we can help LGBT+ students, please imagine this interaction in which you offer suggestions and support. What would you say to this student? Please write down your answers.”
Conclusion		Duration: 1 minutes 10 seconds Timestamps: 48.45-49:55	Acknowledging the advisory board representatives from the LGBT+ community for their input and feedback

^a^LGBT+: lesbian, gay, bisexual, and transgender people. The “+” symbol represents individuals whose identities do not fit typical binary notions of male and female (nonbinary).

^b^All intervention elements are drawn from empirical evidence. We present timestamps and specific content which is included in the multimedia intervention resource.

^c^UNICEF: United Nations Children's Fund.

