## Methods

### Participants and Recruitment

We plan to collect data exclusively from teachers or counselors working in Romanian public schools. All participants will be required to speak Romanian because of the language used in the intervention and measures. Participants who complete the intervention will be sent a participation certificate which could be used for continuing education credits and are given the option to enter a raffle where they can win a 500 RON (equivalent to US $110) gift certificate.

Our recruitment strategy is to ask the local Center for Educational Resources and Assistance to distribute a message nationally, to all their members who are teachers or counselors employed in Romanian schools. If interested, they have the opportunity to sign up for 1 of the several sessions depending on their availability. The sessions are capped at 30, with an average of 25 participants signing up for each (range 24-27). We will advertise a total of 17 sessions across 3 months at different times during the day.

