### Study Design

This intervention’s experimental design is an RCT. We use a 2-group random assignment design, such that participants are randomly assigned to either the experimental condition in which they receive the intervention first and then complete the outcome measures, or to a control condition in which they complete the outcome measures first and then receive the intervention. From an ethical perspective, we chose this design so that all participants will receive the intervention and associated resources by the end of their participation. From a validity perspective, the outcome measures of those in the control condition are not affected by the intervention, thus serving as an appropriate control comparison to participants in the experimental condition.

Participants will join sessions in groups of up to 30 participants, depending on their availability. Cluster randomization will be done at the session level, such that each session will be randomly assigned to either experimental or control conditions. Individual randomization within the session is not possible given that the intervention will be presented to all participants at the same time. Sessions will be scheduled across different times and days outside typical working hours, so we do not anticipate any systematic biases arising from participants’ session choices. To ensure experimental control, each session will be led by 2 researchers who deliver scripted instructions, answer questions, and ensure all participants complete the study at a similar pace and with minimal distraction.

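### The completers-only rule lets the intervention's content decide who has outcomes in the experimental arm, because outcomes follow the intervention there and precede it in the control arm

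*Protocol article*

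**What the plan says.** Data Exclusion, under Statistical Analysis, fixes the analysis set: "We will use data from all participants who completed their participation in the study, without any exclusions". The same section plans one-way between-subjects ANOVAs comparing the arms.

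The Methods paragraph of the Abstract gives the order of events. For one arm, "The experimental group participants will receive the intervention first and then complete the outcome measures"; for the other, "the control group will complete the outcome measures first and then receive the intervention". Study Design repeats this order, states that whole sessions are randomised, and rests the validity of the comparison on control outcomes being untouched by the intervention. All measures are taken in that one session, so no teacher has both a pre-intervention and a post-intervention attitude score in the main comparison.

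The last entry of Table 1 reads "Timestamps: 48.45-49:55", so an experimental teacher sits through just under 50 minutes, including two writing exercises, before the first outcome item. Attrition is mentioned only for the follow-up at 6 to 8 months.

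**The concern.** The sentence claims that nobody is excluded, yet restricting to completers is itself an exclusion made after randomisation. It would do little harm if leaving were unrelated to the arm and to attitude. Here both links are plausible: the content concerns the attitude being measured, and only experimental teachers see it before they are measured.

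Study Design covers half of the issue. The content cannot affect the control answers, but it can affect which experimental teachers are still present to answer. If those who leave hold less favourable attitudes, the remaining experimental teachers look more favourable than the control teachers even when the intervention does nothing. The planned ANOVA cannot correct this, because experimental leavers have no earlier attitude score to adjust for or impute from.

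**Working it through.** **Step 1. What the rule does to a teacher who leaves because of the content.** *Completed* can be read in two ways.

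| Reading of *completed* | Experimental leaver | Control leaver | Consequence |
|---|---|---|---|
| Outcome measures given | No outcomes, not analysed | Outcomes already given, analysed | Selection by the content in one arm only |
| Whole session finished | Not analysed | Outcomes given but discarded | Selection in both arms; equal only if leaving is alike in both |

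The two problems belong to different readings and do not add up. Under the second reading the arms finish the same material in a different order, which may partly balance the selection. However, control teachers reach the content having already answered the questionnaires, and nothing makes their rate of leaving equal to that of experimental teachers.

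**Step 2. Possible size.** The documents give no dropout figure to reproduce, so the proportion leaving is an assumption.

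- Scale: a standard normal outcome, higher being more favourable, with zero true effect.
- p: proportion leaving the experimental arm before outcomes; no such loss in the control arm (first reading).
- Perfect selection: the least favourable p leave. The mean of those who remain is shift = φ(z_p) / (1 − p), where z_p is the p-quantile and φ the normal density.
- Imperfect selection: if the tendency to leave correlates r with the outcome, shift = r × φ(z_p) / (1 − p).

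| p | φ(z_p) / (1 − p) | r = 1 | r = 0.5 |
|---|---|---|---|
| 0.05 | 0.103 / 0.95 | 0.11 SD | 0.05 SD |
| 0.10 | 0.1755 / 0.90 | 0.195 SD | 0.10 SD |
| 0.20 | 0.280 / 0.80 | 0.35 SD | 0.175 SD |

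**Step 3. Comparison with effects named in the article.** The Power section plans on d = 0.66. A shift of 0.195 to 0.35 SD is 30% to 53% of that (0.195 / 0.66; 0.35 / 0.66). At r = 0.5 it is 15% to 27% (0.0975 / 0.66; 0.175 / 0.66). The Introduction cites changes of one-third to one-half of an SD; only the most extreme case in the table reaches the lower end of that range.

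**Step 4. The second reading.** If 20% left experimental sessions and 10% left control sessions, both under perfect selection, the shifts would partly cancel: 0.350 − 0.195 = 0.155 SD would remain. They cancel fully only if the two arms lose the same kind of teacher in the same proportion.

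**The case against.** The best defence is that dropout may be small. Teachers consent after detailed information. Two researchers run each session and keep participants moving together. The certificate and raffle reward completion. The Discussion asks for later work with a wider range of initial attitudes, which hints that strongly negative teachers were few. Control teachers may also leave early: the listed scales total 121 items (10 + 25 + 12 + 16 + 10 + 7 + 3 + 5 + 7 + 10 + 16), many of them explicit about homosexuality. All of this stands, and it means the true shift could be negligible. It does not make the rule sound, since the rule gives no means of showing that the shift is negligible.

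A second objection is that the whole-session reading is the more symmetric one, so retaining control leavers could make the bias worse. That is correct if retention is the only change, and it is why the fix pairs retention with bounds.

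A third is that an article may leave flow tables and sensitivity analyses to a fuller document. That is fair for the tables, but the analysis set is stated here, and stated in a form that conditions on completion.

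A reader might also infer from the counts that most sign-ups are missing from the analysis: 17 sessions at 24 to 27 sign-ups make 408 to 459, against 175. The documents do not support this. The 175 are those randomised: "A sample of 175 school teachers will be randomly assigned to either the control or experimental group". The 17 sessions are only advertised: "We will advertise a total of 17 sessions across 3 months at different times during the day". Since 175 = 7 × 25, fewer sessions may have run. Any gap arises before the completers rule acts and does not measure dropout.

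**Conclusion.** The concern holds for the analysis set. As written, the rule conditions on a post-randomisation event that the content can influence, and that comes before outcome measurement in one arm only. Under either reading of *completed*, the randomised comparison is not protected.

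The size is unknown. The range of 0.20 to 0.35 SD rests on an assumed loss of 10% to 20% from the experimental arm alone, with perfect selection on attitude. At correlation 0.5 it is 0.10 to 0.18 SD, and with less or more even dropout it is smaller still. It would be wrong to conclude that the trial has suffered this bias, or that its direction is known; the article gives no completion figures by arm.

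The point should be settled before analysis. The Results section says that data collection has ended and that analysis waits for acceptance of the protocol, so the rule can still be changed without sight of the results.

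**What to change.** - Define the analysis set as every teacher who joined a randomised session, in the arm of that session. Use all available outcomes, including those of control teachers who left later and completed scales from partial responders.
- Report, by arm and session, how many joined and how many gave outcomes.
- Prespecify Lee trimming bounds for any arm difference in outcome completion, and present them with the main comparison. If proportions c (control) and e (experimental) give outcomes and c > e, trim a share (c − e) / c of the control outcomes from one tail and then from the other. This assumes that being assigned to see the content first moves teachers only one way, towards missing outcomes. Without the bounds, retaining control leavers leaves the selection one-sided.
- Show whole-session completers as a sensitivity analysis, and say what *completed* means there.
- Compare control leavers with control stayers only if departure was recorded against the anonymous responses.
- Separately, reconcile the Abstract, Participants and Recruitment, and Power on the number of sessions actually run.

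The cost is revised wording, one flow table and one additional analysis, with no new data collection. The bounds may be wide if completion differs by arm. They also depend on attendance counts having been kept, which the article does not say; if they were not, that should be reported as a limitation.

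### Sessions are randomised, but the planned 1-way ANOVAs ignore session, so the F tests and P values are anti-conservative whenever within-session correlation is above zero

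*Protocol article*

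**What the plan says.** **Randomisation.** Study Design in the protocol article states: "Cluster randomization will be done at the session level, such that each session will be randomly assigned to either experimental or control conditions". It then rules out the alternative: "Individual randomization within the session is not possible given that the intervention will be presented to all participants at the same time". Sessions hold up to 30 people and are led by two researchers.

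**Sessions.** Participants and Recruitment says: "We will advertise a total of 17 sessions across 3 months at different times during the day". Teachers choose a session by availability, with an average of 25 sign-ups each (range 24 to 27). The Abstract gives a sample of 175. The Power section gives 122, with over-recruitment up to 200.

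**Analysis.** Data Exclusion, the section that also holds the hypothesis tests, says: "we will perform a series of 1-way between-subjects ANOVAs to compare attitudinal, cognitive, behavioral, and affective outcomes" between participants in the two conditions. One adjustment is named, "while controlling for contact with LBGT+ individuals", for one group of measures (printed as effective, presumably affective). F tests and P values will be reported, "as well as all descriptive statistics (n, mean, and SD"). Violin plots are planned "to visually represent means, CIs, as well as score distributions for each outcome"; how the CIs are calculated is not stated.

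The article contains no session effect, cluster-robust variance, session-level analysis, ICC or design effect.

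**The concern.** A 1-way between-subjects ANOVA with condition as its only factor assumes independent participants. Here the independently randomised units are sessions. Teachers in one session picked the same time slot, sat together, and had the same two researchers answering questions and setting the pace. Any resulting similarity in their answers adds between-session variance to the comparison of arms, and the ANOVA error term leaves it out.

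The degrees of freedom show the gap. On 175 teachers the ANOVA uses 175 − 2 = 173 error degrees of freedom, while 17 sessions support at most 17 − 2 = 15. All four hypotheses in Aims and Hypotheses rest on these tests, so false-positive claims are at stake across the attitudinal, cognitive, behavioural and affective outcomes.

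This is not a detail that an article leaves to a fuller plan. The article names the test, and the test does not match the stated randomisation.

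**Working it through.** **1. The plan's own figure.** The only related figure is the sample size of 122 for d = 0.66 and power 0.80. Alpha is not stated; two-sided 0.05 and equal arms are assumed. The individual-level t-test calculation gives 76 in total (74 by the normal approximation), so 122 is not reproduced. It matches power 0.95 instead. The ratio 122/76 ≈ 1.6 could absorb a design effect of that size (ICC about 0.025 at 25 per session), but the article does not present it as a clustering allowance and attributes over-recruitment to multiple outcomes. In any case a larger sample does not correct the type I error of a test that ignores session.

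**2. Inputs.** N = 175 (Abstract); 17 sessions and 25 sign-ups per session (Participants and Recruitment). ICC is not given; 0.01, 0.02, 0.05 and 0.10 are assumed.

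**3. Formulas.** With m teachers per session, the design effect is DE = 1 + (m − 1) × ICC. A nominal two-sided 5% test that ignores it has true type I error 2 × [1 − Φ(1.96/√DE)].

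**4. Main case: 175 teachers over 17 sessions**, m = 175/17 = 10.29. Example at ICC 0.05: DE = 1 + 9.29 × 0.05 = 1.46; 1.96/√1.46 ≈ 1.62; type I error ≈ 10.5%.

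**5. Sensitivity case: sessions of 25**, 175/25 = 7 sessions. Example at ICC 0.05: DE = 1 + 24 × 0.05 = 2.20; 1.96/√2.20 ≈ 1.32; type I error ≈ 18.6%.

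| ICC | DE, m = 10.29 | Type I error | DE, m = 25 | Type I error |
|---|---|---|---|---|
| 0.01 | 1.09 | 6.1% | 1.24 | 7.8% |
| 0.02 | 1.19 | 7.2% | 1.48 | 10.7% |
| 0.05 | 1.46 | 10.5% | 2.20 | 18.6% |
| 0.10 | 1.93 | 15.8% | 3.40 | 28.8% |

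**6. Check by simulation** (20,000 null trials per setting). In the same ICC order, the ANOVA rejected in 6.3%, 6.9%, 10.1% and 15.6% of trials with 17 sessions of 10, and in 8.1%, 10.9%, 19.0% and 29.0% with 7 sessions of 25. A t test on session means stayed at about 5% throughout. At ICC 0 both tests were at about 5%. With 17 sessions of 25 the ANOVA gave 7.8%, 10.8%, 18.6% and 28.7%, so the inflation follows session size rather than the number of sessions.

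**7. Power of a valid test.** The session-mean t test at d = 0.66 has power of about 97%, 96%, 92% and 83% with 17 sessions of 10, and 87%, 81%, 66% and 47% with 7 sessions of 25.

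**The case against.** The strongest reply is that the correlation may be small. Sessions are ad hoc groups gathered after a national message, not intact schools. The content is recorded, the instructions are scripted and the exercises are individual writing tasks. Control participants complete the outcomes before the intervention, so shared delivery cannot create correlation in that arm. The article also expects no systematic bias from session choice.

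Much of this stands, and it limits the claim. A reader might infer that every F test, P value and interval is too favourable. That requires a positive ICC for every outcome; the article gives none, and at zero there is no inflation. But nothing in the article supports assuming zero. Self-selection by time slot and shared session conditions apply in both arms, and the remark on systematic bias concerns the estimate, not correlated answers.

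Three further inferences are tempting and not supported:

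- **That type I error is near 29%.** This needs both an ICC of 0.10 and sessions of 25. The average of 25 counts sign-ups, not completers, and 7 sessions is a derived figure. The article's own numbers do not settle it: 17 × 25 = 425 exceeds both 175 and 200.
- **That the effect estimates or a planned interval for Cohen d are wrong.** Ignoring session does not bias the mean differences, and no interval for d is planned. CIs are mentioned only for the violin plots, without a method; they would be too narrow only if built from individual-level SDs.
- **That session membership is certainly known.** Ethical Considerations says the data are anonymous, and no section says a session identifier is stored.

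**Conclusion.** The mismatch is real and should be corrected before analysis: the unit of randomisation is the session, and the stated tests treat teachers as independent. The F tests and P values are anti-conservative whenever the within-session correlation is above zero, as are any CIs built from individual-level SDs. For assumed ICCs of 0.01 to 0.10, a nominal 5% test has a true type I error of about 6% to 16% on the 17 advertised sessions, and about 8% to 29% in the sensitivity case of 25 per session. These ranges rest on the assumed ICCs, a two-sided 5% level, roughly equal session sizes and 175 analysed teachers. The number and size of the sessions actually held are not known from the article.

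**What to change.** **Change.** For each outcome, replace the 1-way ANOVA with a linear mixed model: arm as fixed effect, session as random intercept, Kenward-Roger or Satterthwaite degrees of freedom. Use the same model for the contact-adjusted analyses, and for the analyses by LGBT+ status where it is estimable; few teachers per session in one stratum may prevent that. A t test on session means with sessions minus 2 degrees of freedom is a simpler alternative for the unadjusted comparisons. It is not a strict equivalent when session sizes differ, and it does not directly carry the individual-level contact adjustment. Report the number of sessions per arm and the ICC for each outcome, and use session-adjusted CIs, including in the violin plots.

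**Cost.** Data collection has ended, but the Results section says analysis waits for protocol acceptance. The change is therefore analysis work only, provided a session identifier is stored in or recoverable from the anonymous data. The investigators should confirm this first.

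Intervals widen by about √DE × (t quantile on sessions − 2 df)/(t quantile on 173 df):

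- 17 sessions: √1.09 × 2.131/1.974 ≈ 1.1 times at ICC 0.01, and √1.93 × 2.131/1.974 ≈ 1.5 times at ICC 0.10.
- 7 sessions: √2.20 × 2.571/1.974 ≈ 1.9 times at ICC 0.05, and √3.40 × 2.571/1.974 ≈ 2.4 times at ICC 0.10, with power at d = 0.66 down to about 66% and 47%.

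That loss reflects the information the design holds at those ICCs; the ANOVA would hide it.

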**Education** **[9]**			
	Definition of terms	Duration: 05 minutes 40 seconds Timestamps: 02.50-08.30	Definition of LGBT+ terms Definition of sexual orientation Differentiation between sex versus gender Definition of intersex Description of gender identity and transgender
	Threat reduction	Duration: 03 minutes 40 seconds Timestamps: 08.30-12.10	LGBT+ children and their families: meta-analysis on children raised by LGBT+ families Sexuality and sexual orientation in humans and animals. Normalizing varied sexual orientations across species The function of same-sex sexual behavior in ensuring survival
	Effects of stigma to understand minority stress [1]	Duration: 05 minutes 35 seconds Timestamps: 12.10-17.45	Suicide rates of LGBT+ youth The role of stress from exposure to prejudice, ridicule, physical, and verbal aggression in understanding mental health outcomes The role of social support and family or school acceptance in improving mental health and the danger of conversion therapy Bullying as a special case of discrimination, types of bullying, the role of sexual orientation
	Behavioral tools [11]	Duration: 04 minutes 00 second Timestamps: 24.45-28.45	Presentation of tools that can be used by teachers, including the following: Romania’s new antibullying law and bullying protocol in schools Lesson plans to discuss and combat bullying in the classroom UNICEF^c^ intervention model for bullying Procedure to report bullying and harassment with the Romanian National Council for Combating Discrimination Support groups for LGBT+ students in Romania For all resources links were shared in the presentation and then sent in PDF format to all participants

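### The contact covariate for the affective outcomes appears to be recorded after training in one arm and before it in the other, and the plan does not say whether the adjusted or unadjusted analysis decides hypothesis 4

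*Protocol article*

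**What the plan says.** The Study Design section of the protocol article sets out two sequences: "the experimental condition in which they receive the intervention first and then complete the outcome measures" and "a control condition in which they complete the outcome measures first and then receive the intervention". The abstract's Methods paragraph gives the same order and adds that the attitudinal, behavioural, cognitive and affective data "will be collected during the same session (before or after the intervention, depending on the condition"). No separate baseline step is described for either arm.

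Contact is one of the items under Demographic and Control Variables, a subsection of Outcomes: "We will ask participants how often they have contact (eg, talk) with a gay man, a lesbian woman, a bisexual woman or man, or a" (the list closes with transgender people). Answers run over six points from almost daily (1) to never (6). The article gives no time point for the item and no instruction to count only contact before the session.

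The analysis is described under Data Exclusion. The hypotheses are to be tested by one-way ANOVAs between the arms for all four outcome domains, affective included. A following sentence says that for certain measures (printed as effective, evidently meaning affective) the analyses will be done "while controlling for contact with LBGT+ individuals". The article does not say whether this replaces the unadjusted ANOVA or is added to it.

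**The concern.** A covariate is safe to adjust for in a randomised comparison when treatment cannot have moved it. Under the sequence described, the experimental arm would answer the contact item after the training and the control arm before it.

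The training contains material that could influence the answer. Table 1 lists definitions of terms, including "Description of gender identity and transgender", and then 15 minutes of recorded testimonials classed as indirect contact. A teacher who has just seen these may recognise, recall or be willing to report contact that an untrained teacher would not.

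If reported contact rises with training and goes with warmer affect, the adjusted difference is too small. If reported contact falls, it is too large. Either way the adjusted analysis no longer estimates the randomised effect on affect, which is the subject of hypothesis 4. Because the plan does not name the deciding analysis, the affected one could become the main result.

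**Working it through.** **Timing.** Three facts are set side by side.

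1. Study Design and the abstract give two steps per arm, in opposite order.
2. Contact is placed within Outcomes, with no time point of its own.
3. The timing sentence in the abstract names the four outcome domains and does not name the control variables.

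Facts 1 and 2 make it most natural to read contact as part of the single battery. Fact 3 leaves open that it was asked at the start in both arms. The timing is an inference.

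**Size.** The documents give no slope and no shift, so there is no stated figure to reproduce. The only input they supply is the planning effect, d = 0.66, from the Power section. The rest is assumed:

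- b, the within-arm standardised slope of affect on reported contact: 0.3 to 0.5.
- s, the shift in reported contact caused by training, in SD: 0 to 0.3.

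Contact is taken as recoded so that higher means more contact, and the outcome so that higher means warmer affect. With a linear model and a common slope:

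adjusted effect = total effect − b × s

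| b | s | b × s | adjusted effect (0.66 − b × s) | share of 0.66 |
|---|---|---|---|---|
| any | 0 | 0 | 0.66 | 0% |
| 0.3 | 0.1 | 0.03 | 0.63 | 4.5% |
| 0.3 | 0.3 | 0.09 | 0.57 | 13.6% |
| 0.5 | 0.1 | 0.05 | 0.61 | 7.6% |
| 0.5 | 0.3 | 0.15 | 0.51 | 22.7% |

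If s is negative, the same amounts are added to the effect.

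**Check of the formula.** A simulation of 400,000 records with a true effect of 0.66 and b = 0.3 gave adjusted effects of 0.660 at s = 0, 0.600 at s = 0.2 and 0.510 at s = 0.5. The formula gives 0.66, 0.60 and 0.51.

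**The case against.** The strongest reply is that the article never says contact was asked after training. The timing sentence does not cover control variables, these have their own heading, and item order is something a condensed article may leave out. This stands to the extent that post-training collection cannot be asserted as fact. It does not dispose of the point, because the article does fix an order of measurement, does name the covariate, and describes no earlier step.

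Second, an unadjusted comparison of the affective outcomes is already planned, and Cohen d from means and SDs also reads as unadjusted. This is correct. A reader might infer that affect is analysed only with adjustment, and the text does not support that. What remains is that neither analysis is named as the deciding one.

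Third, a session of about an hour cannot change how often someone talks with gay, lesbian, bisexual or transgender people. This also stands. Only reporting can shift, and the documents give no evidence that it does, so zero belongs in the range.

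Fourth, with at most 17 sessions, randomised whole, chance imbalance in contact is plausible and adjustment would guard against it. That is a real benefit. But if contact was asked after training in one arm, an arm difference could be chance or a training effect, and the data could not separate the two.

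A reader might extend the concern to religiosity and ideology, which sit under the same heading. Neither enters any analysis described in the article, so their timing biases nothing planned. A reader might also extend it to the planned split by LGBT+ status. The wording does not settle whether that means the respondent or the group being rated, so nothing firm can rest on it.

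**Conclusion.** The point holds in a limited form. On the plan as written, the contact covariate appears to be recorded at different times relative to training in the two arms, and the plan does not say which affective analysis decides hypothesis 4. The possible bias in the adjusted analysis runs from 0 to 0.15 SD, at most about 23% of d = 0.66. This rests on assumed slopes of 0.3 to 0.5 and shifts of 0 to 0.3 SD, a linear model and a common slope. It is zero if contact was asked before training in both arms, or if training does not alter reporting. The unadjusted ANOVAs are not affected.

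A larger relative figure is tempting. Setting 0.15 SD against the one-third of an SD at the low end of the range in the Introduction gives 0.15 / 0.333 = 45%. That pairs the largest assumed bias with the smallest cited effect, and the documents give no ground for that combination.

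**What to change.** Add to the analysis section:

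1. Hypothesis 4 is decided by the comparison of arms not adjusted for contact.
2. The contact-adjusted analysis is a sensitivity analysis, reported beside the mean of contact in each arm.
3. The report states when the contact item was asked. If it was asked before training in both arms, the adjusted analysis is free of this bias and can be read as such.

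Data collection is reported as complete and the analysis as still to come, so the remedy lies in the analysis and its reporting. Changing the order of the items could not help this trial.

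The text costs about a sentence for the deciding analysis and one for the timing. Statistically, the deciding analysis gives up some precision and some protection against chance imbalance in contact between the few randomised sessions. The sensitivity analysis shows how much the result depends on that choice, although arm means of contact alone cannot tell imbalance from a shift in reporting.
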